H1: If perceptual disturbances in AN and BN are related to biased cognitions about gaining weight rather than to gustatory deficits or BMI, then AN and BN patients should respond with similar sensory performance but higher response bias scores in a discrimination test, (1) compared to non-ED underweight, normal-weight and illness-recovered controls, and (2) during a swallowing compared with a sip-and-spit condition.H2: If fear of weight-gain in restricting-type AN elicits taste aversion, then facial electromyographical, facial expression, and autonomic and subjective correlates of disgust (Kappas, 2003; Kreibig, 2010) while tasting high-sweet and high-fat foods should be observed compared to (1) stimuli of low-sweet and low-fat foods; (2) non-ED underweight, normal-weight, illness-recovered controls and (3) BN patients; and (4) especially during the swallowing compared with the sip-and-spit condition.H3: If avoidance of energy-rich foods in BN reflects a cognitive preoccupation about the increased liking of very sweet tastes associated with gaining weight, then facial electromyographical, facial expression, and autonomic and subjective correlates of pleasure (Kappas, 2003; Kreibig, 2010) while tasting high-sweet foods should be observed compared to (1) fat and low-sweet stimuli; (2) non-ED underweight, normal-weight, illness-recovered controls and (3) restrictive-type AN; and (4) no differences between swallowing and sip-and-spit conditions.

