The experimental session will be composed of assessments of thirst and hunger levels, the Thought-Shape Fusion Body State Scale (TSF-B state) and Brief Mood Scale (BMS) questionnaire, a training session to habituate to the testing environment and apparatus, and either the discrimination of two-alternative forced-choice (2AFC) test in study 1 or multiple-sip temporal-liking (MSTL) with taste reactivity (TR) task in study 2. Each experimental session will take around 1.5 h. Concerning the first study (Table 3), the 2AFC test with signal detection theory (SDT) analysis will be used as it provides a high level of power for small food differences and low levels of response bias (Hautus et al., 2009). On the one hand, the 2AFC test is a psychophysical method in which participants are required to select the one of two food samples, which represents the specified attribute best (e.g., the sweeter one). On the other hand, SDT is a sophisticated tool that permits to understand the information processing that takes place in the brain during sensory discrimination testing, providing an accurate index of perceived sensory differences and efficient characterization of cognitive strategy. Therefore, SDT is critical for investigating maladaptive cognitions involved in the processing of received taste information, which affects sensory testing (Smeets et al., 2008). Furthermore, whether and how much gustatory performance depends on low BMI or psychopathology will be examined including under- and normal-weight controls and patients at different stages of the disorder (currently-ill vs. recovered). Finally, in addition to the sip-and-spit condition, a swallow test condition will be included (Eiber et al., 2002) to enhance cognitive bias toward weigh gain underlying the fear of swallowing and quantify the impact of these biased cognitions on gustatory performance. The 2AFC task will be conducted using the SIPM™ software (Sussex Ingestion Pattern Monitoring, version 2.0.11), in which pairs of two samples (with varying levels of sweetness and fatness), presented simultaneously at each trial, are judged in terms of taste identity and intensity (see Table 2).

**Table 3 T3:** Experimental design of the study 1.

**Group**	**Pre-test**	**Test: two-alternative forced-choice task**	
		**Spit condition**	**Swallowed condition**

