R-AN	Training session to habituate to the testing environment	A vs. B, A vs. C, A vs. D, B vs. C, B vs. D, C vs. D	A vs. B, A vs. C, A vs. D, B vs. C, B vs. D, C vs. D
C-AN			
U-CT			
N-CT			
R-BN			
C-BN			

*A, B, C, D, samples of ice cream with a high-/low-sweet and high-/low-fat taste. The order of the paired samples and conditions (swallow and spit) will be randomized. R-AN, recovered anorectic; C-AN, currently ill anorectic; U-CT, underweight control; N-CT, normal weight control; R-BN, recovered bulimic; C-BN, currently ill bulimic. R-AN and R-BN will be assessed at discharge*.

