### Food samples

In contrast to pure tastes commonly used in research on gustatory perception, four ordinary, more ecologically valid mixtures of chocolate ice cream containing low vs. high levels of fatness and low vs. high levels of sweetness (Table 5) will be presented in 100-ml disposable Styrofoam cups at room temperature and in counterbalanced order across participants. Chocolate ice cream was selected according to the assumptions that chocolate ice cream is likely to be a forbidden food for AN and BN participants, and that AN participants can be expected to have strong aversive associations. The samples are stored at minus 18°C. Optimal mixtures were elaborated at the School of Agricultural, Forest and Food Sciences (Department of Food Science & Management; Bern University of Applied Sciences) and obtained considering previous studies on taste sensory and hedonic ratings (Sunday and Halmi, 1990) and surface response method (Drewnowski et al., 1987b) in AN and BN. Assuming an all-or-nothing (i.e., dichotomous) approach to food in AN and BN, regardless of the fat or sucrose levels, the specific ingredients of the samples were further selected in order to increase differences across ice cream samples in terms of sweetness, creaminess, expectation of caloric content and hedonic reactions (Table 6). In this sense, although previous studies have found pronounced aversion to the sugar-fat mixtures in AN patients, variability in aversive scores across combinations of sweet taste and fat together has also been demonstrated. For instance, differences comparing liking response profiles as a function of increasing sucrose content (0–20% wt/wt) separately from different fat samples (0.1–52.7% fat wt/wt) have been observed in AN (restrictive) and bulimic patients, and in both currently-ill and recovered patients (e.g., Drewnowski et al., 1987b; Sunday and Halmi, 1990). Finally, while water will be used as control stimulus, two savory (high-fat and low-fat) sauces will be added in study 2 as additional comparators to demonstrate that any differences detected are unique to sweet-fat foods in BN patients as previous research suggests.

**Table 5 T5:** Characterization of the food samples with low and high content of fatness and sweetness.

**Components**	**Low fatness and low sweetness**	**Low fatness and high sweetness**	**High fatness and low sweetness**	**High fatness and high sweetness**
Dry matter (%)	30.0	30.0	39.5	39.5
Fat content (%)	1.2	1.2	11.4	11.4

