### Study design

The present international and multi-center research uses a quasi-experimental, cross-sectional design with concurrent controls aims at comparing gustatory perception and hedonics of taste among six groups of participants: R-AN, C-AN, U-CT, N-CT, R-BN, and C-BN, under two counterbalanced conditions of testing: sip-and-spit vs. swallow test condition. The use of a rigorous quasi-experimental design with a well-established type of psychopathology represents an important approach in the experimental psychopathology literature (Zvolensky et al., 2013), particularly in the context of eating disorders for both ethical and pragmatic reasons. However, the limitations are related to the lack of random assignment into groups, which leads to non-equal test groups, which can limit the generalizability of the results to a larger population. In order to reduce the impact of this limitation, threats to validity will be minimized controlling the following factors: comorbidity, stage-of-illness, age-at-onset, duration of illness and time in treatment, depressive mood, craving for food, biased cognitions about weight, current hunger, thirst and food familiarity. In addition, age-matched and weight-matched controls (to the extent possible) will be included in the research design to increase the chances of finding differences between groups. Additional controls by limiting our inclusion criteria are not envisaged as this would make it even more difficult to obtain samples of adequate size (therefore reducing statistical power) and limiting the generalizability (and hence the external validity) of the study protocol.

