#### Planned analysis

Analyses will be adjusted for covariates, namely the scores of EDE-Q, BDI-II, FCQ-T-Reduced, TSF-T-Reduced, and hunger and thirst levels. Additional covariates can be added to the model if necessary. In study 1, the procedure for computing the variance of d′, confidence intervals for d', chi-square tests of significance for d′ and comparisons of multiples d′s among groups across two testing conditions will be performed for sweetness, creaminess and caloric content scores according to the Bi et al. (1997) and Bi (2008) approach. Analogous to d′, confidence intervals, hypothesis tests and multiple comparisons for C and ß will be constructed according to Kadlec's (1999) approach.

In study 2, differences in T–I parameters (Imax, Tmax, AUC), self-ratings (hedonic, familiarity) and intensity of facial expressions (emotion, valence and actions units), as well as the cardiovascular, electrodermal and facial electromyographic outcomes, will be analyzed using mixed, three-way factorial ANOVAs with group (six levels) as between-subjects and testing condition (swallowing vs. sip-and-spit) and food sample (four levels) as within-subjects' factors. Additionally, a time series emotional analysis for assessing emotional responses to beverages will be applied to automated facial expression data using the Wilcoxon signed-rank test (Crist et al., 2016) if more sensitive analysis are needed to detect differences between groups. Outcome variables will be checked for normal distribution. Note that linear mixed models to analyse the data can be envisaged to have more statistical power to detect actually existing study effects and to lead to less biased results in the case that the intraclass correlation coefficient and the design effect show dependency in the data (Hox, 1998). Statistical analyses will be conducted using SPSS (IBM, SPSS; Version 23.0, Chicago, IL, USA). Descriptive statistics will be presented using Mean ± *SD* for all continuous variables.

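### Swallow and spit share one session with no washout described, yet condition order is absent from the stated Study 2 model, its balance within the six groups is unstated, and no hunger re-rating between conditions is described

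*Protocol article*

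**What the plan says.** All references are to the protocol article.

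- **One session, both conditions.** The Procedure section describes one experimental session for each study: "Each experimental session will take around 1.5 h". Tables 3 and 4 give every group both a spit and a swallow column. No break or washout between them is described.
- **Order.** The footnote to Table 3 (Study 1) says: "The order of the paired samples and conditions (swallow and spit) will be randomized". The Study design section says the six groups are compared "under two counterbalanced conditions of testing: sip-and-spit vs. swallow test condition". The footnote to Table 4 (Study 2) does not mention condition order. The Food samples section has the samples presented "at room temperature and in counterbalanced order across participants". None of these places says that condition order is balanced within each group.
- **Model.** Planned analysis gives Study 2 a three-way mixed ANOVA with six-level group between women and, within women, "testing condition (swallowing vs. sip-and-spit) and food sample (four levels". Order, period and sequence are not among the factors or the named covariates. Hunger and thirst are among the covariates.
- **Timing of the ratings.** The Procedure section says: "The experimental session will be composed of assessments of thirst and hunger levels", followed by the state questionnaires, training and the test. It describes no repeat between conditions.
- **Hypotheses.** H1(2) and H2(4) predict a swallow-spit difference. H3(4) predicts "no differences between swallowing and sip-and-spit conditions".

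**The concern.** In effect this is a two-period crossover within each group. The protocol varies the order of the conditions but leaves order out of the stated analysis, and three hypotheses rest on the contrast concerned.

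Two effects need to be kept apart. The first is period drift, such as fatigue, habituation or growing familiarity with the samples, which affects whichever condition comes second. The second is carry-over, meaning what a particular condition leaves behind. Carry-over is plausible on the protocol's own reasoning. The Procedure section adds swallowing in order to heighten concern about weight gain, and it offers patients relaxation at the end of the session because tasting may raise anxiety. It describes nothing of that kind between the conditions.

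At stake are the precision and possible bias of the swallow-spit contrast, and its comparison across groups as small as 10 women per study.

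**Working it through.** The protocol gives no figure for drift or carry-over, so there is none to reproduce. Group sizes per study come from Sample size calculation: 15, 15, 10, 10, 15 and 15 (total 80). All effect sizes below are assumptions in arbitrary outcome units.

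**Set-up.** Let τ be the true swallow-minus-spit contrast, π the drift added in the second condition, cS the carry-over from swallow into a following spit, cP the carry-over from spit into a following swallow, and p the share of a group that swallows first.

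- Swallow first: difference = τ − π − cS
- Spit first: difference = τ + π + cP
- Group mean = τ + (1 − 2p)π + (1 − p)cP − p·cS

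**1. Drift with balanced order (p = 0.5).** The mean is unbiased, but individual differences are shifted by −π or +π. Without an order by condition term, this adds π² to the error variance of the difference. With assumed π = 0.4 and a standard deviation of 1 for the difference otherwise, the variance is 1 + 0.16 = 1.16. The standard error is √1.16 = 1.077 times as large, or about 8% more.

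**2. Drift with unequal order.** A fraction |1 − 2p| of π enters that group's condition effect and so the group by condition interaction.

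| Split | Fraction of π | Bias at π = 0.4 |
|---|---|---|
| 7:8 (closest possible in 15) | 1/15 = 0.067 | 0.03 |
| 7:3 in 10 | 0.40 | 0.16 |
| 11:4 in 15 | 7/15 = 0.467 | 0.19 |

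If order were assigned by unrestricted randomisation, a split of 7:3 or worse in a group of 10 has probability 2 × 176/1024 = 0.34. A split of 11:4 or worse in a group of 15 has probability 2 × 1941/32768 = 0.12. Counterbalancing within each group would make these probabilities irrelevant.

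**3. Carry-over with balanced order.** The bias is (cP − cS)/2.

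- τ = −1, cS = −0.4, cP = 0: result −0.8 (attenuated)
- τ = −1, cS = +0.4, cP = 0: result −1.2 (exaggerated)
- τ = 0, cS = −0.4 or +0.4, cP = 0: result +0.2 or −0.2 (a false difference)
- τ = 0, cS = cP = −0.4: result 0

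In the special case where a fraction k of the swallow response persists into the spit condition (cS = kτ, cP = 0), the contrast becomes (1 − k/2)τ. It is 25% smaller at k = 0.5 and 50% smaller at k = 1.

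**4. What an order term does.** The two orders' mean differences themselves differ by 2π + cS + cP. The order by condition interaction takes this out of the error, and weighting the two orders equally stops an unequal split from leaking into the group comparison. The average of the two mean differences is still τ + (cP − cS)/2, so carry-over bias remains. The order main effect compares the women's totals and estimates cS − cP, but only between women and therefore imprecisely.

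**5. Hunger and thirst.** One value per woman cancels from her own swallow-spit difference. An interaction of the covariate with condition lets the difference vary with starting hunger, but still says nothing about change during the session.

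**The case against.** The strongest reply is that order is already handled by design. Randomized and counterbalanced are compatible words, since women can be randomized to counterbalanced sequences, and with balanced order drift cancels from the mean. Planned analysis also allows further covariates and envisages linear mixed models, and an article may leave a period term to a fuller plan. Only a small amount is to be swallowed (Safety aspects), which limits fullness. Study 2 includes water in each condition as a control stimulus.

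Much of this stands, and it rules out several stronger readings that a reader might infer:

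- **That order is unbalanced within groups.** The protocol does not say so; balance within groups is simply unspecified. The imbalance probabilities need unrestricted randomisation, whereas Study design says counterbalanced.
- **That hunger is rated only once.** This is not stated. Table 2 lists thirst and hunger with the pleasantness ratings rather than as a baseline measure, so repeats are not excluded. They are just not described.
- **That carry-over shrinks the contrast and so favours H3(4).** This needs a real contrast and carry-over of the same sign as the swallow response. If the predicted null is true, unequal carry-over creates a false difference and works against H3(4).
- **That a first-condition-only comparison could settle H3(4).** With about 7 versus 8 women with current BN, power is about 0.15 at an assumed d of 0.5 and 0.30 at 0.8. A non-significant result would be likely even with a real difference.

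The reply does not answer the rest. Counterbalancing removes drift from the mean but not from the error of a model without order, and it does not remove unequal carry-over. A general permission to add covariates does not pre-specify an order by condition term. A small amount swallowed limits fullness more than fear of weight gain. A later analysis plan cannot recover ratings that were never taken.

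**Conclusion.** The point holds as a gap in a stated model and procedure. It is not a demonstrated bias. Order is varied by design but omitted from the Study 2 ANOVA, balance within groups is unstated, and no hunger or thirst rating between conditions is described. The consequences are:

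- some loss of precision (about 8% in the standard error at the assumed drift);
- leakage of 7% to 47% of any drift into a group's condition effect at the splits shown;
- a possible carry-over bias of (cP − cS)/2 in the contrasts behind H1(2), H2(4) and H3(4), of unknown sign.

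Attenuation is the likely result only if the swallow response persists with the same sign. These sizes rest on assumed drift and carry-over, because the protocol gives none. The change is worth making because it costs so little.

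**What to change.** 1. State one order scheme for both studies: condition order counterbalanced within each of the six groups.
2. Add order and its interactions with condition and group to the Study 2 ANOVA, or period and sequence terms if the mixed model is used. The order by condition term is the one that removes drift from the error. Take order into account in the Study 1 comparisons of d′, C and ß as well, for example by stratifying.
3. Re-rate hunger and thirst before the second condition and use condition-specific values.
4. Report first-condition-only results as descriptive support, not as a decision rule for H3(4). State that an order term does not itself remove carry-over.

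Cost: one allocation list per group and about a minute of ratings. Order and order by group use 1 + 5 = 6 degrees of freedom between women, so the error falls from 80 − 6 = 74 to 68. The matching interactions with condition use another six in the condition stratum.

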### Statistical and analytic plan

#### Sample size calculation

Sample size calculations were based on findings of small to medium effects on eating behavior in patients with anorexia and bulimia by our group (e.g., Munsch, 2014) using the software G^*^Power (version 3.13). Assuming two-sided tests with Alpha = 0.05, Beta = 0.2, and effect size *f* = 0.20, the required sample size would be 80 to ensure a power >0.80 in each one of the two studies with a sample distribution of N_C−AN_ = 15, N_C−BN_ = 15, N_R−AN_ = 10, N_R−BN_ = 10, N_U−CT_ = 15, and N_N−CT_ = 15. To obtain the required number of 50 patients per study and taking into account a participation rate of 80% and a dropout rate of 20% in the patient population, a total of 60 patients per study will be needed. Based on our recruitment and testing experiences in Switzerland and Luxembourg (average annual recruitment of 35–40 AN and 35–40 BN patients), the access to a sufficiently powered sample of patients seems to be guaranteed. Finally, in order to achieve the sample size suggested by the power analysis, a sample of 30 healthy controls (university students) per study will be recruited in Fribourg.

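### Study 2 defaults to a repeated-measures ANOVA and allows an optional switch to a linear mixed model on a data-based check with no threshold; the mixed model should be fixed in advance as primary

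*Protocol article*

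**What the plan says.** All references are to the protocol article.

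- **Default model (Planned analysis).** Study 2 outcomes are to be analysed with "mixed, three-way factorial ANOVAs with group (six levels) as between-subjects and testing condition (swallowing vs. sip-and-spit) and food sample (four levels" as within-subjects factors.
- **Alternative (same section).** The text notes that "linear mixed models to analyse the data can be envisaged to have more statistical power" and to give less biased results, "in the case that the intraclass correlation coefficient and the design effect show dependency in the data". It gives no cut-off for either quantity and does not say whether the dependency meant is between one person's tastings or between participants at one centre.
- **Design (Study design).** Everyone is tested "under two counterbalanced conditions of testing: sip-and-spit vs. swallow test condition".
- **Stimuli (Food samples).** Chocolate ice cream was chosen partly because "AN participants can be expected to have strong aversive associations".
- **Software (Planned analysis).** "Statistical analyses will be conducted using SPSS (IBM, SPSS; Version 23.0, Chicago, IL, USA". The article does not say how a missing cell is handled.

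**The concern.** Two things follow from this wording.

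First, the choice between two models rests on statistics computed from the trial's outcomes, with no rule for reading them. Even when they point to dependency, the mixed model is only something that can be considered. Two competent analysts could follow the text and report different primary models. If the check is about repeated tastings, it asks a question that the design has already answered.

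Second, the default is fragile when cells are missing. A repeated-measures ANOVA in SPSS uses complete rows only. This is a general property of the procedure and is not stated in the article. A participant who declines one tasting would then lose all eight cells for that outcome. Missing cells are plausible here because the foods were selected to be difficult for some patients. Groups in Study 2 are only 10 to 15 people.

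**Working it through.** **1. Does the undefined trigger matter?**

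Analysed cells per person: m = 2 conditions × 4 samples = 8. Design effect = 1 + (m − 1) × ICC = 1 + 7 × ICC, so a cut-off of 2 means an estimated ICC above 1/7 ≈ 0.14. Two plausible readings of the trigger were simulated (80 participants × 8 cells, 2,000 runs each):

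| True ICC | 5% test of ICC fires | Design effect > 2 fires |
|---|---|---|
| 0.05 | 67% | 0.1% |
| 0.10 | 98% | 10.5% |
| 0.20 | 100% | 90% |
| 0.30 | 100% | 100% |

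At low to moderate ICC the reported model depends on which unstated rule is used.

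**2. The plan's own figure.**

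The article gives N = 80 per study at f = 0.20, "Assuming two-sided tests with Alpha = 0.05, Beta = 0.2". It does not give the test family, number of measurements or correlation, so 80 cannot be uniquely reproduced. With six groups and an assumed correlation of 0.5, the group-by-within interaction needs 86 (m = 2), 64 (m = 4) or 45 (m = 8). The figure is not disputed here. The m = 4 setting is used below only to scale the loss.

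**3. Complete cases if missingness is scattered.**

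Share complete = (1 − p)^8, where p is an assumed missing rate per cell, independent across cells and equal in all groups. Power is for the group-by-within interaction, with noncentrality f² × N × m/(1 − ρ), m = 4 and ρ = 0.5. At N = 80 this is 0.04 × 80 × 4/0.5 = 25.6 on 15 and 222 degrees of freedom.

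| p (assumed) | (1 − p)^8 | Complete of 80 | Power |
|---|---|---|---|
| 0 | 1 | 80 | 0.91 |
| 1% | 0.923 | 74 | 0.88 |
| 3% | 0.784 | 63 | 0.80 |
| 5% | 0.663 | 53 | 0.70 |

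**4. Complete cases if refusal is concentrated.**

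Suppose only the 15 currently ill anorexia (C-AN) participants refuse, and only swallowed cells. At 14%, 15 × 0.14 = 2.1 people are lost; at 26%, 15 × 0.26 = 3.9. About 78 or 76 of 80 remain, although C-AN itself falls from 15 to about 13 or 11. Sections 3 and 4 are alternative assumptions and must not be added together.

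**5. Direction of bias among completers.**

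Two-cell model for C-AN; all values are assumptions: spit-cell elevation 0.80, true swallow-minus-spit effect 0.40 with person-to-person SD 0.5, person SD 0.8, residual SD 0.6 (spit-cell variance 0.64 + 0.36 = 1).

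*Refusal depends on the observed spit response* (logistic, slope 1.5):

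| Refusal | Completers: elevation (true 0.80) | Completers: contrast (true 0.40) | Likelihood, all observed cells: contrast |
|---|---|---|---|
| 14% | 0.64 | 0.46 | 0.40 |
| 25% | 0.52 | 0.50 | 0.40 |

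The contrast rises by regression to the mean: the residual share of spit variance, 0.36, times the drop in the spit mean. This is 0.36 × 0.16 ≈ 0.06 and 0.36 × 0.28 ≈ 0.10, which matches the table.

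*Refusal depends on the swallowed response itself*, which is then not observed:

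| Refusal | Completers: contrast (true 0.40) | Likelihood, all observed cells: contrast |
|---|---|---|
| 12% | 0.32 | 0.28 |
| 22% | 0.26 | 0.19 |

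Here both are biased, and the likelihood estimate of this contrast slightly more so.

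**The case against.** The strongest reply is that the planned ANOVA already treats condition and sample as within-subjects factors, so it does model the correlation between one person's tastings. That is right: a reader might infer that the default ignores dependency, and the text does not support this. The reply continues that in a multi-centre study the ICC and design effect may refer to clustering by site. That reading is possible. The check would then not be redundant, but it would still be undefined and made on the outcome data.

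A reader might also infer that the plan drops from the study anyone with a missing cell. The article does not say so. Deletion is inferred from the procedure and software, applies outcome by outcome, and could be avoided by a missing-data rule in a document not shown.

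A third tempting reading is that complete-case analysis works against H2 as a whole. It does not follow. When refusal depends on observed responses, the C-AN elevation is understated but the swallow-minus-spit contrast, which is part (4) of H2, is overstated. Nor do the documents establish that refusals will cluster in particular cells. The quoted expectation of aversion concerns anorexia only, H3 predicts pleasure in bulimia, and Safety aspects describes small amounts and measures to reduce distress.

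Finally, a mixed model is not a general cure. It does not remove bias when refusal depends on the unobserved swallowed response. It recovers neither people who drop out entirely nor the facial-expression data of those who decline filming.

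**Conclusion.** The point holds as a cheap improvement. What rests on the text alone is that the Study 2 model may be changed after inspecting the outcomes, on a criterion without a threshold, towards a method that the article itself credits with more power and less bias. What rests on inference is the per-outcome loss of participants with a missing cell.

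The size of that loss is not fixed by the documents. It ranges from about 2 to 4 people under concentrated refusal in C-AN to 27 of 80 (80 − 53) under 5% scattered missingness, and every rate is an assumption. The bias can run in either direction, depending on the contrast and on the reason for refusal. The case for the mixed model is that it uses all observed cells, is valid when missingness depends on observed responses, and removes an uncontrolled choice. It does not repair every form of missing data.

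**What to change.** In Planned analysis, for Study 2:

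1. Name the linear mixed model as the primary analysis for all outcomes: fixed effects for group, condition, food sample and their interactions; participant random effects with a stated covariance structure; all observed cells used; and a small-sample degrees-of-freedom method confirmed to be available in the named SPSS version, such as Satterthwaite.
2. Delete the ICC and design-effect trigger. If clustering by centre was the worry, add site as a fixed effect.
3. Keep the three-way ANOVA as a sensitivity analysis.
4. State that the mixed model assumes missingness depends on observed data, and report missing cells by group, condition and sample so that readers can judge this.

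The cost is wording. The method and the software are already named, and no data collection changes. The small downside is that a covariance structure, and a fallback if the model does not converge, must be written down in advance.
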